#### IRT Modeling

Although CFA together with internal reliability tests can be more than sufficient to validate scales for use in research and evidence-based practice, IRT modeling can be a considerable complement when used with CFA [51]. In our planned analysis, an IRT approach to item reduction and final item selection will follow a staged workflow integrating Mokken scale analysis (MSA) as a nonparametric technique and parametric IRT graded response models (GRMs), supported by dimensionality assessment and local-dependence diagnostics [52,53]. MSA, together with the EFA results, will be used as the initial screening step to identify candidate item sets that demonstrate adequate scalability along a common latent trait and support the development of short forms with robust ordering properties. Specifically, scalability will be evaluated using Loevinger’s coefficients at the item level (Hi) and scale level (H), and reliability will be summarized [54]. Monotonicity and (where targeted) invariant item ordering will be examined using standard Mokken diagnostics to detect items with substantive violations (eg, nonmonotone response functions or marked ordering inconsistencies). Items showing weak scalability, notable monotonicity violations, or poor ordering behavior will be deprioritized, particularly when they provide redundant content relative to stronger items, while maintaining conceptual coverage across the domain.

GRM-based IRT will then be applied as the confirmatory and refinement step for the candidate item set(s) retained from MSA. Dimensionality will be evaluated to ensure each subscale is sufficiently unidimensional to support GRM estimation. Local item independence will be assessed via residual correlations (correlations among item residuals after accounting for the latent factor); item pairs showing elevated residual correlations will be interpreted as potential local dependence (eg, redundancy or shared wording) and will trigger content review, with prioritization of removing the weaker item. For each subscale, GRMs will be estimated to quantify item discrimination and category threshold functioning; item characteristic curves and test information functions will be used to evaluate category performance and the contribution of each item to measurement precision across the targeted trait range. Final selection will prioritize items with adequate discrimination, ordered and well-spaced thresholds, complementary information profiles, minimal local dependence, and preserved content balance.

#### Reliability Estimates and Test-Retest Reliability

Internal consistency reliability for the PRIDE scale will be evaluated within each sample (United States and Europe) and reported for each subscale, and for the total scale only if a defensible higher order or general-factor model supports total scoring. Reliability will be quantified using Cronbach α and, for ordinal Likert-type items, ordinal alpha (α_ord) computed from a polychoric correlation matrix. In addition, McDonald omega (ω) will be estimated for each monotone or unidimensional subscale using a congeneric factor model (allowing heterogeneous item loadings) and will be treated as the primary model-based estimate; where relevant, omega estimates derived under an ordinal framework (polychoric correlations or appropriate ordinal estimators) will be reported. Item-total correlations will be examined to assess the contribution of individual items to subscale reliability, and items with low item-total correlation (eg, <0.30) will be flagged for potential removal in conjunction with evidence from MSA, CFA (factor loadings or model fit), and IRT GRM outputs (discrimination, thresholds, and information), in accordance with the prespecified item selection rules. Test-retest reliability correlations will establish temporary (2-wk) stability of the PRIDE Scale using the blinded combined United States and European samples pooled. The test-retest sample size power calculation suggested an ideal sample size of 62 for this reliability test.

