## Methods

### Scale Development and Measures

The PRIDE Scale included 39 new test items examining LGBTQI+ health care knowledge, awareness, attitudes, skills, and the work environment,. Development of these items was iterative and generated through literature reviews, expert consultation, and adaptation from existing scales. The Delphi method was used to select the most relevant items via iterative rounds of feedback from an expert panel. The first step was to identify and recruit a diverse group of international experts with relevant experience in LGBTQI+ health care, psychometric scale development, and clinical competence. These experts included health professionals (mostly physicians and psychologists), LGBTQI+ health advocates, clinicians, researchers, public health professionals with expertise in biostatistics and epidemiology, and educators. In total, the panel was comprised of 12 members. There were 3 Delphi rounds. In the first round of item generation, experts on the study team developed a broad number of items (100) both from the existing literature and newly formed items, which were then randomly listed and presented to the expert panel. Experts were asked to evaluate each item based on its relevance, clarity, and its potential importance for measuring LGBTQI+ related competencies among health care professionals. Experts could also comment on each item and suggest new or adapted items. After the first round, responses were scored for relevance and ordered accordingly. Quantitative consensus was defined a priori as a threshold of ≥75% and a median rating of ≥4 on a 5-point scale indicating an item as important or very important. These thresholds align with accepted Delphi standards and ensure that retained items reflect high agreement and rating stability. Based on the scoring (1-100), 39 items that showed strong consensus for inclusion were retained. These items are measured on a 5-point Likert-style scale that ranges from 1 (strongly disagree) to 5 (strongly agree).

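### Any total PRIDE score would get only Cronbach alpha and ordinal alpha, which for a multidimensional total show neither its overall reliability nor its general-factor share

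*Protocol article*

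**What the plan says.** All of this comes from the Protocol article, section Reliability Estimates and Test-Retest Reliability, unless another section is named.

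- **When a total gets a reliability figure.** Subscales are the default. Reliability is given "for the total scale only if a defensible higher order or general-factor model supports total scoring".
- **General coefficients.** "Reliability will be quantified using Cronbach α and, for ordinal Likert-type items, ordinal alpha (α_ord) computed from a polychoric correlation matrix".
- **Omega.** "McDonald omega (ω) will be estimated for each monotone or unidimensional subscale using a congeneric factor model". The same sentence makes it the primary model-based estimate. The ordinal version follows in that sentence, with no extension to a total: "where relevant, omega estimates derived under an ordinal framework (polychoric correlations or appropriate ordinal estimators) will be reported".
- **Other reliability evidence.** A 2-week test-retest correlation is planned for the scale.
- **Content.** Under Scale Development and Measures: "The PRIDE Scale included 39 new test items examining LGBTQI+ health care knowledge, awareness, attitudes, skills, and the work environment". So there are five content areas, one of which concerns the employer and not the respondent. The items use a 5-point response format.
- **Model criteria.** The section EFA and CFA lists global fit indices for confirming the exploratory structure. No measure of general-factor strength is named there or in the reliability section.

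**The concern.** The plan uses its preferred coefficient where the score is simplest and leaves the harder case to the two alphas. A total that needs a higher-order or general-factor model to justify it is a sum over several factors, and two questions then arise. How reliable is the sum? How much of it reflects the one general trait that a single score implies? Alpha answers neither. It counts variance shared only within a domain towards its value, so it can be high when the domains have little in common. Yet it does not count all of that variance, so it also falls short of the reliability of the sum.

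What is at stake is interpretation. The Discussion expects the instrument to serve as a research outcome and a self-assessment tool. If a total is published with an alpha in the high 0.80s, users could take that as support for one PRIDE score even where the general factor is weak. A weak general factor is plausible here, because the total would combine a clinician's own competence with the perceived climate of the workplace.

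**Working it through.** The plan states no reliability value or target, so there is no figure of its own to reproduce. The check compares the three coefficients under a higher-order model.

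**Inputs.** The documents give 39 candidate items and five content areas. They do not give the final number of items, the loadings or the factor correlations. *Assumed:* k = 30 retained items, five domains of n = 6, equal loadings λ = 0.65 (λ² = 0.4225), equal factor correlation φ, and standardised items with uncorrelated errors.

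**Formulas.** V is the sum of the item correlation matrix, that is, the variance of the total:

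- V = k + λ²·Σn(n−1) + λ²φ·(k² − Σn²)
- alpha = k/(k−1) × (1 − k/V); ordinal alpha is the same expression on the polychoric matrix
- omega-total = 1 − k(1 − λ²)/V
- omega-hierarchical = λ²φk²/V

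**Constants.** Σn(n−1) = 5×30 = 150. Σn² = 5×36 = 180. k² − Σn² = 900 − 180 = 720. Error variance = 30×0.5775 = 17.325.

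**Example, φ = 0.2.** V = 30 + 63.375 + 60.84 = 154.215.

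- alpha = 30/29 × (1 − 30/154.215) = 0.83
- omega-total = 1 − 17.325/154.215 = 0.89
- omega-hierarchical = 0.4225×0.2×900/154.215 = 76.05/154.215 = 0.49

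| φ | V | alpha | omega-total | omega-hierarchical |
|---|---|---|---|---|
| 0.2 | 154.2 | 0.83 | 0.89 | 0.49 |
| 0.3 | 184.6 | 0.87 | 0.91 | 0.62 |
| 0.4 | 215.1 | 0.89 | 0.92 | 0.71 |
| 0.7 | 306.3 | 0.93 | 0.94 | 0.87 |

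In each row alpha lies below omega-total and above omega-hierarchical. The distance to omega-hierarchical is large at low φ and small at φ = 0.7.

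**Sensitivity.** With all 39 items in domains of 8, 8, 8, 8 and 7 and λ = 0.6:

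- φ from 0.1 to 0.3 gives alpha 0.80 to 0.88, omega-total 0.86 to 0.91 and omega-hierarchical 0.31 to 0.62.
- φ = 0.7 gives alpha 0.94, omega-total 0.94 and omega-hierarchical 0.87.
- Cronbach alpha simulated on skewed 5-point items is slightly lower, at 0.78, 0.83 and 0.86 for φ = 0.1, 0.2 and 0.3.

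With 20 items (five domains of 4, λ = 0.6, φ = 0.2), alpha is 0.73 and omega-hierarchical 0.45. The level drops but the gap remains.

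**Can a well-fitting model hide a weak link?** Return to the 30-item case. Let four competence factors correlate 0.5 with each other and 0.1 with a climate factor. Second-order loadings of 0.71 for competence and 0.14 for climate reproduce these correlations exactly (0.71×0.71 = 0.5; 0.71×0.14 = 0.1). Then:

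- V = 93.375 + 0.4225×36×(12×0.5 + 8×0.1) = 196.8, so alpha = 0.88.
- omega-hierarchical = [0.65×6×(4×0.7071 + 0.1414)]²/196.8 = 134.15/196.8 = 0.68.
- The general factor explains 0.1414² = 2% of the climate factor.

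A perfect fit therefore says nothing about general-factor strength.

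**The case against.** The strongest case on the other side has four parts.

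*Domain-specific common variance is reliable variance.* This is correct, and it limits the point. A reader might infer that alpha would make an imprecise total look precise. The documents and the arithmetic do not support that. At φ = 0.2 omega-total is 0.89 against an alpha of 0.83, so alpha errs on the low side for precision. What can be weak is the reading of the total as one trait.

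*The condition on total scoring is itself a safeguard.* It is, and a weak general factor is the case it should screen out. A reader might also infer that totals would be admitted on fit indices alone. The plan does not say so; the indices are listed for confirming the exploratory structure. What remains is that *defensible* has no stated criterion for strength.

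*No PRIDE total is promised.* True. The total mean score described under Scale Development and Measures belongs to the LGBT-DOCSS. The harm needs both a reported total and a weak general factor, and with a strong one the gap is small.

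*A condensed article may leave such detail to the full plan.* This would carry weight if the article were silent. It is not: it names the coefficients and limits omega to subscales that are unidimensional or monotone, as quoted above. Any numeric floor is a different matter. The documents supply no basis for one, and none is claimed here.

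The planned test-retest correlation does not fill the gap, because stable domain-specific variance counts as reliable there too.

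**Conclusion.** The point holds as a modest one about choice of coefficient. It is not an error or a contradiction in the plan. If a total is reported, the named internal-consistency coefficients are the two alphas, and for a multidimensional total they answer neither relevant question. In the 30-item case with φ from 0.2 to 0.4, alpha falls 0.03 to 0.06 below omega-total and exceeds omega-hierarchical by 0.18 to 0.34. At φ = 0.7 the excess is 0.06. These sizes rest on assumed loadings, correlations and item numbers, since the documents give none. The direction holds in every scenario examined. The consequence is possible, not certain: a high alpha could be taken as support for a single score that the general factor does not carry.

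**What to change.** In Reliability Estimates and Test-Retest Reliability, add that for any total score the following apply:

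- Omega-total (overall reliability) and omega-hierarchical (general-factor share) will be reported from the higher-order or bifactor model that the section already requires, with alpha and ordinal alpha secondary.
- Omega-hierarchical will be part of judging whether that model supports total scoring. If the authors want a numeric floor, they should choose it before the analysis, which the Results section places in Summer 2026.

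The cost is a sentence or two and one extra output from a model that has to be fitted anyway; no new data are needed. The downside is that the general-factor figure will be lower than alpha.

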As the use of convenience sampling (eg, through professional networks, institutional contacts, and online platforms) can introduce selection bias, to evaluate sample representativeness, the demographic profile of respondents in each country will be compared against available national health care workforce statistics. To ensure reproducibility of all data management and analytic procedures, a fixed random seed will be set prior to all data manipulation steps (seed=123,456). Prior to splitting, early respondents will be identified within each country as the first 25% of participants by enrollment order, to allow subsequent assessment of early responder bias. The sample will then be randomly split 50/50 within each country, with participant order randomized using a uniform random variable to remove any time- or motivation-related ordering effects, yielding Split A as the estimation subsample for EFA and Split B as the holdout subsample for CFA. Balance between the 2 subsamples will be verified for country distribution, LGBTQI+ identity status, and the proportion of early respondents, both overall and within each country, using cross-tabulations and Fisher exact tests. Limitations associated with convenience sampling, including potential volunteer bias and overrepresentation of professionals with prior interest in LGBTQI+ inclusive practice, will be explicitly acknowledged and considered in interpreting the generalizability of the validation findings.

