#### EFA and CFA

EFA will be conducted to examine the underlying dimensional structure of the PRIDE scale and to inform item retention. As an initial parametric approach, EFA will be performed using principal component analysis (PCA) with varimax (orthogonal) rotation to obtain a simple and interpretable factor solution. Prior to extraction, the suitability of the data for factor analysis will be assessed (eg, inspection of the correlation matrix and standard measures of sampling adequacy). The number of factors to retain will be determined using the Kaiser criterion (eigenvalues ≥1) in conjunction with visual inspection of the scree plot to identify the point of inflection. Items will be evaluated based on their pattern of loadings, and only items with primary factor loadings ≥0.40 will be considered for inclusion. Items showing substantial cross-loadings (eg, ≥0.30 on more than 1 factor) or weak or unstable loadings will be reviewed for removal or revision, with decisions guided by both statistical evidence and conceptual coherence with the intended constructs. Given the ordinal nature of Likert-type responses, a complementary nonparametric ordinal approach will also be implemented. Specifically, a polychoric correlation matrix will be estimated and subjected to factor analysis with varimax rotation, applying the same factor-retention rules (eigenvalues ≥1 and scree plot) and item-selection criteria (primary loading ≥0.40, limited cross-loading). Consistency of the factor structure across the PCA-based and polychoric-based solutions will be examined to strengthen inferences regarding dimensionality and to ensure that the final factor model is robust to distributional assumptions. We acknowledge that PCA is technically a data-reduction technique that accounts for total item variance rather than modeling shared latent variance exclusively, and therefore does not constitute a latent variable model in the strict sense [30,44]. Its use here is pragmatic, consistent with its established role as an initial item-selection tool at the exploratory stage. The robustness of the dimensional solution will be evaluated formally through the planned cross-validation against the polychoric-based factor solution and, most importantly, through the subsequent CFA with maximum likelihood estimation, which will constitute the primary evidence for the latent structure of the PRIDE Scale.

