CFA will be used to confirm the factor structure identified in the EFA. Model fit will be evaluated using the following indices: chi-square statistic, comparative fit index (CFI), root mean square error of approximation (RMSEA), standardized root mean square residual (SRMR), Tucker-Lewis index, Akaike information criterion, and Bayesian information criterion will be used following cutoff recommendations by Hu and Bentler [45,46].

To establish the cross-cultural and cross-demographic equivalence of the PRIDE Scale, formal measurement invariance testing will be conducted using multigroup confirmatory factor analysis. Following the sequential approach recommended by Vandenberg and Lance [47] and Putnick and Bornstein [48], configural invariance (same factor structure across groups), metric invariance (equal factor loadings), and scalar invariance (equal item intercepts) will be tested sequentially across two sets of planned comparisons: (1) Italian-speaking and English-speaking (United Kingdom and United States combined) subsamples, to establish cross-linguistic and cross-national measurement equivalence; and (2) LGBTQI+ and cisgender heterosexual participants, to evaluate whether the scale functions equivalently across groups that differ in sexual orientation and gender identity; a particularly important consideration given the nature of the construct being measured. Model comparisons will be evaluated using the chi-square difference test and changes in CFI (ΔCFI ≤−0.010) and RMSEA (ΔRMSEA ≤0.015) as criteria for invariance [49]. Additional subgroup analyses will be conducted to assess the potential influence of professional background (student vs trained practitioner) and gender on the validity of the CFA solution [50]. Where measurement invariance testing reveals a failure of scalar invariance for specific items, differential item functioning (DIF) analyses will be conducted as a planned follow-up to identify items performing differently across subgroups. DIF will be evaluated using ordinal logistic regression, which enables the detection of both uniform and nonuniform DIF for polytomous Likert-type items. Items exhibiting significant and practically meaningful DIF will be flagged for review during subsequent scale refinement.

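### CFA evidence may help remove items, so the CFA holdout (Split B) could shape the scale it is meant to confirm, with no unused data left

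*Protocol article*

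**What the plan says.** Under Analytical Methods, "The sample will then be randomly split 50/50 within each country", "yielding Split A as the estimation subsample for EFA and Split B as the holdout subsample for CFA". The two halves use up the sample, so there is no third part.

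Under EFA and CFA, "CFA will be used to confirm the factor structure identified in the EFA". The CFA is also the safeguard offered for starting from principal components, and the article describes it as the analysis "which will constitute the primary evidence for the latent structure of the PRIDE Scale".

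Under IRT Modeling, "an IRT approach to item reduction and final item selection will follow a staged workflow", made up of Mokken scale analysis (MSA) followed by graded response models (GRM). The weaker item of a locally dependent pair may be removed, and "Final selection will prioritize items with adequate discrimination, ordered and well-spaced thresholds, complementary information profiles, minimal local dependence, and preserved content balance". No split is named for either step.

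Under Reliability Estimates and Test-Retest Reliability, items with a low item-total correlation (for example below 0.30) are "flagged for potential removal in conjunction with evidence from MSA, CFA (factor loadings or model fit), and IRT GRM outputs". Internal consistency is evaluated in the United States and European samples, without restriction to Split A.

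**The concern.** A holdout can confirm a scale only if it played no part in choosing the scale's items. Split B is the only sample named for the CFA. If its loadings or fit help decide which items go, the reduced set is then judged on data that helped select it. Item-total screening or GRM refinement run on all respondents has the same effect.

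What is at stake is how the fit indices for the published scale can be read. The article judges fit against published cutoff recommendations. Even a modest upward shift could move a model across a cutoff, and the result would still be presented as holdout confirmation.

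**Working it through.** **Side-by-side reading**

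| Step | Sample stated | Can it remove items? |
|---|---|---|
| EFA | Split A | Yes |
| CFA | Split B, the holdout | Its loadings and fit count as removal evidence |
| Item-total screen | US and European samples | Yes, it is the trigger |
| MSA and GRM | None named | Yes, including local dependence and final selection |
| CFA of the final item set on unused data | Not described | – |

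The second row is the conflict: one analysis is both the confirmation and a source of removal evidence. This does not depend on whether IRT comes before or after the CFA.

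**Sample-size arithmetic** (inputs from Study Population and Sample, and Results)

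- The article's own figures reproduce: 39 × 5 = 195 and 39 × 10 = 390.
- Planned sample: 700 / 2 = 350 per half; 350 / 39 = 9.0 per item.
- Achieved sample: 1339 / 2 = 669.5 per half; 669.5 / 39 = 17.2 per item.

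These counts precede the exclusion of participants with more than 10% of items missing, whose number is not given. At the achieved size, each half exceeds the preferred 10 per item, so selection and confirmation can be kept apart.

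**How large the optimism could be**

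The documents give no number of removed items and no degree of model misfit, so all inputs below are assumptions. Each simulation compares fit in Split B, after items were removed using Split B, with fit of the same items in an independent sample of equal size.

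1. *Item-total trigger only.* Five factors, 39 items, loading screen of at least 0.40 in Split A, then removal of items with Split B item-total correlation below 0.30; n = 669, 60 replicates per scenario. On average 0 to 0.47 items were dropped. Mean CFI in Split B against fresh data was 0.960 vs 0.961, 0.949 vs 0.950, 0.849 vs 0.848 and 0.805 vs 0.806, a difference of at most 0.002. Removal for local dependence was not modelled.
2. *Removal on residuals, one subscale.* Ten items, one factor, loadings 0.45 to 0.75, minor residual correlations (SD 0.06), normal data, three items dropped on Split B residuals, 400 replicates.
   - n = 669: RMSEA 0.061 vs 0.074; CFI 0.971 vs 0.957 (difference 0.014). In 29% of replicates RMSEA was at most 0.06 in Split B but not in fresh data.
   - n = 350: RMSEA 0.055 vs 0.076; CFI 0.975 vs 0.953 (difference 0.022). The corresponding share was 39%.
3. *Heavy removal on residuals and loadings.* Five correlated factors, 39 items cut to 25, n = 669, moderate model error, 60 replicates. Mean CFI 0.951 vs 0.928 (difference 0.023); CFI of at least 0.95 in 52% vs 3% of runs. With negligible model error the optimism was below 0.01.

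The effect therefore runs from nothing visible to about 0.02 in CFI at n = 669, depending on the removal criterion, the number of items dropped and the true misfit.

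**The case against.** The strongest reply is that the removal rule is narrower than it first looks. Low item-total correlation is the trigger, and CFA output is one of three corroborating sources. No sentence removes an item for CFA misfit alone. Items that load at least 0.40 in Split A seldom fall below 0.30 in Split B, and the first simulation shows almost no optimism on that route. If nothing is dropped on CFA or later evidence, Split B remains a valid holdout. All of this stands.

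A reader might also infer that IRT refinement follows the CFA, so that the model confirmed is not the scale published. The article does not establish this. It places Mokken analysis with the EFA results as a first screen, names no split for MSA or GRM, and shows the order in a flowchart (Figure 2) that is not reproduced here. Section order is not analysis order.

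Nor do the larger simulated figures describe this plan, because the article sets out no residual-driven search from 39 to 25 items. The 52% vs 3% contrast partly reflects a threshold of 0.95 lying almost on the simulated mean of 0.951, and the article quotes no such threshold. No simulation here measured optimism in omega or in the invariance tests.

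Finally, the article is condensed and refers to prespecified item selection rules that may be set out elsewhere. Silence on a refit is therefore weak evidence. But admitting CFA output as removal evidence while calling Split B a holdout is stated text, not an omission.

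**Conclusion.** The concern holds in a conditional form. The plan permits item removal on CFA evidence, and on item-total screening not limited to Split A, while naming Split B as the holdout and its CFA as the main structural evidence. If any item goes on that basis, Split B no longer confirms the final scale independently, and the article describes no other data that could.

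The optimism may be negligible if only the item-total trigger operates. It is larger if items are removed on residuals or local dependence in Split B. The simulated differences illustrate that range and do not predict this study's result.

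A reader might go further and conclude that the final item set will certainly never be confirmed on unused data. The documents do not support that: removal is only potential, the order of CFA and IRT is inferred, and the full analysis plan is not shown.

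**What to change.** - Carry out all item reduction in Split A: EFA, MSA, GRM, local-dependence review and item-total screening. State the split for each step.
- Strike CFA loadings and model fit from the evidence for item removal in the reliability section.
- Freeze the item set and factor model, then run the confirmatory CFA on that set once in Split B.
- Label any item change made after seeing Split B as exploratory.
- The abstract says analysis has started, whereas the Results section places it in Summer 2026. If Split B has already been examined, report what was seen and when.

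The cost is wording and order of analysis, with no new participants. Selection would use about 670 rather than 1339 respondents, before exclusions for missing data. That is about 17 per item, above the article's preferred 10, but item parameters used for selection will be less precise. After confirmation, final item parameters, reliability and, if group sizes require it, invariance can be estimated on the full sample.
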